### Maintenance

Using all data sources above, we will identify pragmatic strategies to ensure both high-fidelity program delivery and implementation sustainability. An implementation and sustainability plan will be developed by the end of the study.

### Economic evaluation

To assess, from a health sector and broader societal perspective, the value for money of LISTEN compared to usual care (comparison), a within-trial economic evaluation will be undertaken along with economic modelling.

Detailed costing of the LISTEN intervention will be undertaken using financial data and micro-costing methods. At each time point within the trial, participants will be asked to complete a brief resource use questionnaire to collect information about other healthcare resources used and lost productivity [37, 38]. Participants will also be asked for consent to access their Medicare Benefit Schedule (MBS) and Pharmaceutical Benefits Scheme (PBS) data containing administrative information (numbers and cost details) on visits to health care providers and prescription medication covering the same time frame of study participation.

The AQoL-4D utility values for each participant at each time point will be used to calculate QALYs [45] using the area under the curve method. The within-trial economic evaluation will measure and value any change in healthcare resource use and then compare any additional costs to additional QALYs through an incremental cost-effectiveness ratio (ICER). Bootstrapping will be used to determine confidence intervals for the ICER and construct an acceptability curve to determine the cost-effectiveness of the intervention against the commonly used willingness-to-pay threshold of $50,000/QALY [46]. Sensitivity analyses will be undertaken to evaluate the robustness of results with changes to costing or analytical assumptions.

Scale-up and implementation costs as well as longer-term cost-effectiveness will be estimated based on population-wide modelling techniques based on published epidemiological data.

### Sample size

Based on a brief PST randomised pilot study assessing diabetes distress at 6 months [24] and assuming an alpha of 5%, we estimate requiring a minimum total sample of *N* = 226 (n = 113 per arm). This will enable us to detect an effect size of 0.3 (Cohen’s d) for the primary outcome, diabetes distress, with 80% power. Allowing for a 50% attrition rate observed in a trial with a similar recruitment strategy [47], we aim to recruit a minimum of *N* = 454 participants. Based upon prior experience using the NDSS register for recruitment to a trial [48], with a response rate of 1%, we estimate that recruiting a sample of *N* = 454 participants will require invitations to a random sample of *N* = 45,400 NDSS registrants.

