#### Randomisation

Participants will be randomised (1:1 ratio) to either the intervention (LISTEN) or comparison group (usual care), via central randomisation by computer. The allocation will be fully concealed from the research team including the project manager (RG) and the trial statistician (BH). Upon randomisation, participants will be notified of their group allocation via e-mail by a research assistant independent of the investigator team. Randomisation will be conducted in random permuted blocks of participants, stratified by diabetes type, gender and age (< 60; ≥ 60 years old), in order to minimise imbalances in the group allocation overall and on the specific strata. Once they are allocated to an available HP, participants randomised to the intervention arm will receive a call from the facilitating HP within 1 week (approx.) to arrange sessions. The research team (except SG who will be conducting quality assurance) will remain blinded. Any violation of blinding will be recorded and reported with the main findings.

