#### Primary outcome

The primary outcome is the between-group difference in diabetes distress at T2. Diabetes distress will be assessed using the 20-item Problem Area in Diabetes (PAID) scale. Participants indicate which of the 20 diabetes issues are currently a problem for them, ranging from (0) ‘*not a problem*’ to (4) ‘*a serious problem*’. Item responses are summed and transformed to generate a scale score (0–100), with scores ≥ 40 indicative of severe diabetes distress. The PAID scale is valid, reliable and sensitive to change [32].

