### Planned analyses

Analysis of the primary outcome will be conducted on an intention-to-treat (ITT) basis, using repeated measures analysis of variance (ANOVA), or restricted maximum likelihood mixed-effects models (REML) [49]. The null hypothesis, that there is no difference in the primary outcome between the intervention and comparison groups (at T2), will be assessed using *p*-values for the fixed-effects for the associated covariates in each model, with a *p*-value < 0.05 deemed statistically significant. If participants have missing assessments at T2, the analysis of variance will be replaced by a mixed model analysis using the REML. A per-protocol set (PPS) will include only those participants who engage with all aspects of the study protocol and complete a minimum of one LISTEN session (intervention) or access the web-based resource (comparison) to be used for a sensitivity analysis of the primary endpoint. Secondary outcomes, including psychological distress (K10), general emotional well-being (WHO-5) and coping self-efficacy (CSES) will be analysed as per the primary outcome.

Qualitative data from semi-structured interviews will be de-identified, transcribed verbatim using a professional transcriber and imported into NVivo. Thematic analyses [50] will be used to explore and identify key themes about participant’s experiences of the LISTEN intervention and barriers to, and facilitators of, adoption and implementation.

There are no plans to conduct an interim analysis of the outcomes, as per the statistical analysis plan. Due to the low-risk nature of the intervention, we do not anticipate any harm associated with the intervention for participants, and thus have no stopping rules.

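### 113 analysed per arm does not follow from alpha 5%, d = 0.3 and 80% power for the T2 contrast unless an unstated baseline adjustment with a correlation of about 0.6 is assumed

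*Protocol article*

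**What the plan says.** All of the following is in the protocol article.

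- **Sample size.** The calculation is based on a pilot study that measured diabetes distress at 6 months, "assuming an alpha of 5"%. It arrives at 226 participants, 113 per arm, and concludes: "This will enable us to detect an effect size of 0.3 (Cohen’s d) for the primary outcome, diabetes distress, with 80% power". The number is then raised to 454: "Allowing for a 50% attrition rate observed in a trial with a similar recruitment strategy". The section names no test, sidedness, baseline adjustment or correlation between visits.
- **Primary outcome.** "The primary outcome is the between-group difference in diabetes distress at T2".
- **Planned analyses.** The primary analysis is by intention to treat, using repeated measures ANOVA or a REML mixed model, with REML replacing ANOVA if T2 assessments are missing. The hypothesis is set at one visit: "The null hypothesis, that there is no difference in the primary outcome between the intervention and comparison groups (at T2"). How baseline PAID enters the model is not fixed.
- **Randomisation.** Allocation is 1:1.

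**The concern.** The Sample size section prints an effect size, an alpha, a power and a sample size. A reader who puts the first three into the usual formula for two means gets about 175 per arm, not 113. Rounding cannot explain a gap of that size, so either the power is overstated or the calculation used something that is not on the page.

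Which of the two it is matters for reading the result. The article says the trial will determine whether the programme is effective and should be implemented at scale. If the claimed power depends on baseline adjustment at a particular correlation, it is delivered only if the analysis makes that adjustment and the correlation is that high. Otherwise a non-significant result would be judged against a sensitivity that the trial did not have.

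**Working it through.** **Inputs.** d = 0.3, alpha 5%, 80% power and 113 per arm (Sample size); 1:1 allocation (Randomisation); contrast at T2 (Primary outcome, Planned analyses). Sidedness is not stated. I take two-sided because the null is one of no difference, and also show one-sided. The correlation r between visits is not given, so every value of r below is an assumption.

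**1. The plan's figure from its own inputs.**

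n per arm = 2(1.960 + 0.842)² / d² = 2 × 7.849 / 0.09 = 174.4, so 175. With the t distribution it is 175.4, so 176 (352 in total). One-sided, the t-based figure is 138.1, so 139. Neither gives 113.

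**2. Power and detectable effect at 113 per arm, unadjusted** (noncentral t).

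- Power at d = 0.3: 61.2% two-sided, 72.7% one-sided.
- Detectable d at 80% power, two-sided: 0.374. The normal approximation gives 2.802 × √(2/113) = 0.373.

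**3. The attrition step.** 226 / (1 − 0.5) = 452, against 454 stated. This step is sound, and the gap does not come from it.

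**4. Which analyses would recover 113?**

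*T2 adjusted for baseline.* The variance is multiplied by 1 − r². Setting 174.4(1 − r²) = 113 gives r = 0.59.

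*T0-to-T2 change contrast.* The variance is multiplied by 2(1 − r). Setting 174.4 × 2(1 − r) = 113 gives r = 0.68.

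Power at 113 per arm, d = 0.3, two-sided:

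| Assumed r | T2 adjusted for baseline | T0-to-T2 change |
|---|---|---|
| 0.4 | 69% | 54% |
| 0.5 | 74% | 61% |
| 0.6 | 80% | 71% |
| 0.7 | 88% | 83% |

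*Group effect averaged over three visits.* With f = d/2 = 0.15 and m = 3 visits, the noncentrality is f²Nm / (1 + (m − 1)r). At N = 226 and r = 0.46 this is 0.0225 × 226 × 3 / 1.92 = 7.95, which gives about 80% power. This is not the T2 contrast, and it assumes that the arms already differ by 0.3 at T0, before randomisation.

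**5. Mixed model with dropouts included.** Assumptions: 227 randomised per arm, 113 with T2 data, between 113 and 180 with T1 data, a common correlation r between visits, normal approximation, T2 contrast.

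| Assumed r | Baseline means constrained equal | Baseline means left free |
|---|---|---|
| 0.5 | 74–76% | 67–69% |
| 0.6 | 80–83% | 70–72% |
| 0.7 | 88–90% | 74–76% |

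The treatment of baseline therefore decides whether 80% is reached.

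**The case against.** The strongest reply is that the unadjusted two-sample test is not the planned analysis. The article plans repeated measures ANOVA or REML with three visits, and a mixed-model T2 contrast also uses T0 and T1 data from people who drop out. With baseline means constrained equal and r of about 0.6, such a model delivers 80% power at the full 50% attrition. The article is also a condensed account. The full protocol, the statistical analysis plan and the pilot study are not shown, and any of them may give the correlation.

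Much of this stands. A reader might infer that the trial has only 61% power, that it would miss a true d = 0.3 about 39% of the time, that 352 completers are required, or that the power claim fails once attrition exceeds about 22% (1 − 352/454). The documents do not support any of these as unconditional statements. All four describe the unadjusted comparison only.

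Two things remain. First, the point is not that detail was left out: the article prints a set of figures that do not agree for the contrast it names. Second, a repeated-measures analysis does not by itself close the gap. With baseline means left free, T2 power stays below 80% across r = 0.5 to 0.7. A T0-to-T2 change contrast at r = 0.6, the value that rescues the baseline-adjusted analysis, has only 71%. The Planned analyses section allows all of these.

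**Conclusion.** The point holds in this form: 113 per arm does not follow from alpha 5%, d = 0.3 and 80% power for the between-group contrast at T2. From those inputs alone, 176 per arm are needed; 113 per arm gives 61% power two-sided (73% one-sided), and 80% is reached at d of about 0.374.

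The claim is recoverable. A T2 contrast adjusted for baseline PAID gives 80% at 113 per arm if r is about 0.6. That rests on a correlation the article does not state and an adjustment it does not commit to. If r is 0.4 to 0.5, the same analysis has 69% to 74%.

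This is therefore an unsupported power statement, not proof that the trial is underpowered. The calculations assume a two-sided 5% test, equal variances and 113 per arm with T2 data. If attrition is below 50%, power is higher under every analysis.

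**What to change.** Keep N = 454 and make one of two changes.

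1. **Preferred.** Commit the primary analysis to a T2 contrast adjusted for baseline PAID, or to a mixed model with baseline means constrained equal across arms. In the sample size statement give the method, the sidedness, the assumed T0-T2 correlation (about 0.6) with its source, and the power over a range of r, for example 69%, 74%, 80% and 88% at r = 0.4, 0.5, 0.6 and 0.7.
2. **Otherwise.** Restate the detectable effect: 113 per arm gives 80% power for d of about 0.374 in an unadjusted two-sided comparison. If the 61% power at d = 0.3, the 352 completers or the 22% attrition limit are quoted, label them as applying to the unadjusted comparison only.

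The cost is a change of wording and, under the first option, a firmer commitment in the analysis section. Baseline PAID is already collected, so no participants or assessments are added. The commitment should be fixed before outcome data are examined by arm. Under the second option the stated sensitivity becomes less favourable.

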### Data management

Data from all three timepoints will be downloaded from Qualtrics and linked according to the participant ID. Identifiable information will be separated from study data and stored along with the participant ID number in a password-encrypted Excel spreadsheet. All data will be stored in a secure electronic file accessible only by the research team. In accordance with clinical trial regulations, data will be kept for a minimum of 15 years after study completion before being disposed by erasing of electronic files.

### Planned analyses

Analysis of the primary outcome will be conducted on an intention-to-treat (ITT) basis, using repeated measures analysis of variance (ANOVA), or restricted maximum likelihood mixed-effects models (REML) [49]. The null hypothesis, that there is no difference in the primary outcome between the intervention and comparison groups (at T2), will be assessed using *p*-values for the fixed-effects for the associated covariates in each model, with a *p*-value < 0.05 deemed statistically significant. If participants have missing assessments at T2, the analysis of variance will be replaced by a mixed model analysis using the REML. A per-protocol set (PPS) will include only those participants who engage with all aspects of the study protocol and complete a minimum of one LISTEN session (intervention) or access the web-based resource (comparison) to be used for a sensitivity analysis of the primary endpoint. Secondary outcomes, including psychological distress (K10), general emotional well-being (WHO-5) and coping self-efficacy (CSES) will be analysed as per the primary outcome.

Qualitative data from semi-structured interviews will be de-identified, transcribed verbatim using a professional transcriber and imported into NVivo. Thematic analyses [50] will be used to explore and identify key themes about participant’s experiences of the LISTEN intervention and barriers to, and facilitators of, adoption and implementation.

There are no plans to conduct an interim analysis of the outcomes, as per the statistical analysis plan. Due to the low-risk nature of the intervention, we do not anticipate any harm associated with the intervention for participants, and thus have no stopping rules.

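### The primary null is specific to 6 months (T2), but the plan does not name the T2 contrast as the test that decides it

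*Protocol article*

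**What the plan says.** The target is clear. Under Primary outcome the article states: "The primary outcome is the between-group difference in diabetes distress at T2". PAID is measured at T0, T1 (8 weeks) and T2 (6 months), and T2 is the primary endpoint. Planned analyses repeats T2 in the null hypothesis.

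The decision rule is looser. The primary analysis is by intention to treat, "using repeated measures analysis of variance (ANOVA), or restricted maximum likelihood mixed-effects models (REML"). The null is to be assessed by p-values "for the fixed-effects for the associated covariates in each model", "with a *p*-value < 0.05 deemed statistically significant". A conditional switch follows: "If participants have missing assessments at T2, the analysis of variance will be replaced by a mixed model analysis using the REML". K10, WHO-5 and CSES are to be analysed in the same way as the primary outcome. A separate statistical analysis plan is mentioned but not shown.

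**The concern.** The phrase that carries the decision is plural, names no term, and speaks of covariates where a treatment contrast is expected. More than one p-value from the fitted model could be said to satisfy it.

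The method named first makes this matter. A repeated-measures ANOVA over three visits routinely prints two treatment tests. The group main effect averages the arms over all visits, including the pre-randomisation baseline. The group-by-time interaction has two degrees of freedom and responds to any difference in profile, including one confined to T1. Neither tests a difference at T2.

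The intervention is up to four sessions offered weekly, so an early benefit that fades by 6 months is a pattern the analysis should handle correctly. If an omnibus test decided, such a trial could report a 6-month benefit that is not there. With a real T2 effect, the three-visit main effect would lose power. Because the secondary outcomes follow the primary method, they inherit the same ambiguity.

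**Working it through.** **Inputs from the article.** Alpha: "assuming an alpha of 5" per cent, with sidedness not stated (two-sided assumed here). Effect: "detect an effect size of 0.3 (Cohen’s d) for the primary outcome". Power 80%. Evaluable sample 226, or 113 per arm. Attrition 50%. Visits T0, T1 and T2.

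**Assumptions.** Standardised SD of 1, compound symmetry with correlation ρ from 0.4 to 0.7, complete data at 113 per arm, and no baseline difference. The article gives no correlation.

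**Does the sample size reveal the intended test?** The article says "we estimate requiring a minimum total sample of *N* = 226 (n = 113 per arm"). An unadjusted two-sided comparison at T2 needs 2(1.960 + 0.842)²/0.3² = 174.4, or 175 per arm (350 in total) when rounded up. With 113 per arm its power is 0.62. A one-sided test needs 138 per arm. The stated figure therefore does not follow from the stated inputs alone. It can be reached in at least two ways:

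- Baseline-adjusted T2 comparison: 174.4(1 − ρ²) = 113 gives ρ = 0.59.
- Three-visit average: 174.4(1 + 2ρ)/3 = 113 gives ρ = 0.47.

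So the sample size does not identify the deciding test.

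**Formulas.** Write the arm effects at T0, T1 and T2 as (0, d1, d2). For a single contrast c, the non-centrality is λ = (n/2)(c′d)²/(c′Σc), with n = 113 and n/2 = 56.5.

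- Group main effect: λ = 56.5 × [(d1 + d2)/3]² / [(1 + 2ρ)/3].
- Interaction (2 df): λ = 56.5 × SS/(1 − ρ), where SS is the sum of squares of the three effects about their mean.
- Baseline-adjusted T2 contrast: λ = 56.5 × d2²/(1 − ρ²).
- T2 minus baseline contrast: λ = 56.5 × d2²/[2(1 − ρ)].

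Rejection rates come from the non-central chi-square distribution.

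**Worked case, ρ = 0.5, effect at T1 only (0, 0.3, 0).**

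- Main effect: mean 0.1, λ = 56.5 × 0.01/0.667 = 0.85, rejects 15%.
- Interaction: SS = 0.01 + 0.04 + 0.01 = 0.06, λ = 56.5 × 0.06/0.5 = 6.78, rejects 64%.
- T2 contrast: λ = 0, rejects 5%.

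**Worked case, ρ = 0.5, effect at both visits (0, 0.3, 0.3).**

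- Main effect: mean 0.2, λ = 56.5 × 0.04/0.667 = 3.39, power 45%.
- Interaction: SS is again 0.06, power 64%.
- Baseline-adjusted T2 contrast: λ = 56.5 × 0.09/0.75 = 6.78 on 1 df, power 74%.
- T2 minus baseline: λ = 56.5 × 0.09/1 = 5.09, power 62%.

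**Range over ρ = 0.4 to 0.7.**

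| True effect (T1, T2) | Main effect, 3 visits | Interaction, 2 df | T2 minus baseline | T2, baseline-adjusted |
|---|---|---|---|---|
| 0.3, 0 | 13–16% | 56–86% | 5% | 5% |
| 0.5, 0 | 29–37% | 95–100% | 5% | 5% |
| 0, 0.3 | 13–16% | 56–86% | 54–83% | 69–88% |
| 0.3, 0.3 | 39–49% | 56–86% | 54–83% | 69–88% |

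An F reference with 2 and 448 df lowers the smallest interaction figure from 56% to 55%, hence about 55–86%.

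**The switch.** With 454 to be recruited and 50% attrition planned, about 227 participants are expected to be lost. Some missing T2 data are then practically certain, so the rule sends the analysis to REML. The ANOVA would survive only with complete T2 data.

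**The case against.** A reader might infer that the stated tests are simply not T2 tests, and that the plan will declare false 6-month benefits at the rates above. The document does not support that. The sentence that mentions fixed effects also restricts the null to T2. In a mixed model with visit as a category, the arm effect at T2 is a fixed effect and a valid test of that null. A repeated-measures ANOVA can also carry a planned T2 contrast. The article nowhere names a group main effect or an interaction as the deciding test. The rejection rates therefore belong to one permitted reading and are not error rates of the plan.

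The switch also answers much of the worry about ANOVA discarding incomplete cases and so conflicting with intention to treat, because REML is the near-certain analysis. The trigger mentions only T2, but a trial with T2 complete and T1 incomplete is not realistic at 50% attrition.

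Nor does averaging always cost power. A baseline-adjusted mean of T1 and T2 has 87–96% power for a sustained 0.3 SD effect, above the T2 contrast's 69–88%. The loss is specific to averages diluted by baseline or to effects that arrive late.

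Finally, this is a condensed article. The unseen analysis plan may name the contrast, and the covariance structure and degrees-of-freedom method properly belong there.

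All of this stands. What remains is that the article does state a method, a source for the p-value, a threshold and a switching rule, and together these do not single out the T2 test that its own null requires.

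**Conclusion.** The point holds as a loosely fixed decision rule, not as a demonstrated wrong test. The null is about T2, the deciding p-value is unnamed, and the omnibus tests of the first-named method do not address that null. If one of them decided, a T1-only effect of 0.3 SD would be called significant in about 55–86% (interaction) or 13–16% (main effect) of trials. A T2 contrast holds 5% whatever happens at T1. These figures rest on 113 per arm, compound symmetry, complete data, a two-sided 5% test and an assumed correlation of 0.4 to 0.7. The ANOVA option serves no purpose at the planned attrition. This is a should-fix matter: it governs the main conclusion, but the plan's own wording and its switch already point towards a model in which the right test is available.

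**What to change.** Remove the repeated-measures ANOVA option and the conditional switch. State one primary analysis: a REML mixed model of PAID in all randomised participants, with categorical visit and arm-by-visit terms. Adjust for baseline PAID, either as a covariate or by constraining the baseline means to be equal. Name the single between-arm contrast at T2 as the sole primary test, two-sided at 5%, reported with its 95% confidence interval. Make the T1 contrast secondary, and use the same form for K10, WHO-5 and CSES. The covariance structure and degrees-of-freedom method can stay in the analysis plan.

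The cost is about two sentences in the analysis section, matched in the analysis plan and settled before any unblinded analysis. No new data are needed. Under the assumptions above, baseline adjustment also raises power at T2 to 69–88%, from 54–83% for a change-from-baseline contrast.
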